#### Characteristics of the study population:

Participants will be drawn from the population of HIV-infected patients receiving care at 15 selected health facilities that are part of the ABLE project (see Facilities and Other Resources). We plan to screen approximately 6,900 HIV-infected patients for tobacco smoking and subsequently enroll 750 patients who are interested in quitting tobacco smoking into the trial, 375 of whom will participate in the pre-implementation phase and 375 of whom will participate in the implementation phase across 3 waves of implementation at 5 facilities each. Study participants will receive HIV care and treatment according to national standards. Participants will be eligible to participate in the study if they meet the following criteria:

#### Inclusion criteria:

- (1) HIV-infected
- (2) self-reported daily smoker
- (3) age 18 years and older
- (4) engaged in HIV care as defined by being on ART for at least 6 months
- (5) willing/able to provide informed consent in English or Setswana

#### Exclusion criteria:

- (1) pregnancy or nursing

Informed consent will be administered in the participant's choice of English or Setswana language.

We will ensure ethical conduct of the study through respecting and protecting the interests of all potential and enrolled participants, building trust between researchers and participants, and conducting the study under the principles of good clinical and laboratory practices.

Participant sampling and recruitment: Recruitment activities will begin at the HIV care services through introduction of the study by the lay health worker (LHW)/Case Managers or clinical nurse dispenser/prescribers. Tobacco use screening will occur within the context of HIV outpatient care. The LHW Case Manager will identify individuals who initially screen positive for tobacco use. They will be

linked with a research assistant also stationed in the HIV outpatient clinic who will lead them through the informed consent process and then offer enrollment to those interested in participating in the study. Individuals who present at the study clinic for screening and enrollment will complete the informed consent process on a first come, first serve basis prior to the completion of any study specific activities.

Individuals participating in interviews or focus group discussion for the qualitative analysis will also complete a consent process prior to completion of any study activities. We will randomly select enrolled participants to complete interviews and will recruit individuals who failed to abstain until we reach our target sample size.

Retention: We have maintained high retention rates under the ABLE project, as evidenced by high viral load suppression rate of 99%. We will leverage the current retention approaches under the ABLE project and include additional strategies. Retention strategies include information leaflets about the importance of retention, appointment cards, motivational text messages, and phone calls (and home visits) to remind participants of appointments. All participants who miss study visits will be contacted.

## 2. Sources of Materials

Clinical care material will be obtained through extraction of data, and records, including longitudinal clinical and laboratory measurements, and will be available as part of informed consent for the study from the Integrated Patient Management System (IPMS) and the Patient Information Management System (PIMS); the two main electronic medical record (EMR) systems in use in Botswana. Clinical information with individual identifiers will not be released without the written permission of the participants which will be obtained as part of informed consent.

Research material that will be obtained from living individuals will include breath and data. Data collected will include information regarding demographics and socioeconomic characteristics, medical history, tobacco use, and substance use.

Additional materials include survey questionnaires and assessments administered at different timepoints, as well as focus group discussions and semi-structured interviews. Qualitative data will be digitally recorded, transcribed verbatim and translated into English. When the recordings are not being transcribed, they will be maintained in a locked storage cabinet.

Careful data management procedures will be implemented to ensure unique identification and proper ID linkage for all patient visits, data, clinical, demographic data, biologic specimens, and qualitative data. All

data will be secured in a locked file cabinet and password-protected database accessible only by key study personnel. The sites will maintain appropriate medical and research records for this study in compliance with International Council for Harmonization (ICH) E6, section 4.9 on “Records and Reports,” and regulatory and institutional requirements for the protection of confidentiality of participants.

Any publication about this research study will omit names and any other personally identifiable information. However, individually identifiable private information may be reviewed by the following groups to monitor the conduct of the study and participant safety: The Ministry of Health and Wellness, the HRDC, the National Institutes of Health, the Office of Human Research Protections, and the UMB IRB.

### 3. Potential Risks to Subjects

We expect participant risk to be greater than minimal risk though this is offset by the existing and well-trained expertise of the research staff and clinical staff at the facilities engaged in this study. Potential risks to the subjects are the following:

i. Risk of breach of Confidentiality

There is the potential risk of breach of confidentiality regarding healthcare data, HIV status, and/or smoking status. At each of the steps in the study, we will protect participant privacy and confidentiality to obviate these risks e.g. consenting in private setting, not including names on case report or survey forms, etc.)

ii. Potential risks/side effects of quitting smoking

These include headache and nausea, tingling in hands and feet, coughing and sore throat, increased appetite and associated weight gain, intense cravings for nicotine, irritability, anxiety, and depression.

At each study facility, we will train the nurse prescriber/dispensers directly involved in managing the patients on these issues and identify referral systems to civil society support groups or other healthcare services in in order to ensure that these issues can be adequately addressed. In addition, information on these side effects will be discussed with the patients.

iii. Potential risks/side effects of varenicline:

These include nausea (up to 30%). In addition to nausea, other side effects occurring >5% of clinical trials and twice the rate in placebo were abnormal dreams, constipation, flatulence, and vomiting. Also in rare cases, changes in behavior, hostility, agitation, depressed mood, suicidal thoughts/actions, rash, and sensitivity reactions have occurred.

We will closely monitor for depressive and other neuropsychiatric symptoms and have a careful plan in place for any exacerbation of symptoms or suicidality. All participants will be thoroughly informed of the various side-effects of varenicline, which they might experience and will be appropriately cautioned concerning their activities in the hours after administration. Since participation is voluntary, participants can withdraw at any time if they find the behavioral procedures or drug effects undesirable. Each time a participant receives their medication, the prescribing clinicians will assess for adverse side effects using a standardized questionnaire. If a participant reports depressed mood or suicidal ideation, the participant will receive an immediate evaluation by a qualified clinician to ensure participant safety and proper provision of treatment. Treatment with varenicline will be stopped for any participant experiencing these types of adverse events. Further participation in the study will be decided upon with input from the treating clinician, the research team and the participant.

We are aware that in September 2021 Pfizer voluntarily recalled varenicline (marketed under the brand name Chantix) due to concern that the medication may contain levels of N-nitroso-varenicline above the FDA limit (37ng per day). It is important to note that other makers of varenicline (i.e., Apotex) did not have this problem with their manufacturing of varenicline and remain FDA approved. <https://www.fda.gov/drugs/drug-safety-and-availability/fda-updates-and-press-announcements-nitrosaminevarenicline-chantix>

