#### Training of Nurse prescribers/dispensers on varenicline use

Nurse prescribers will attend a three-day didactic and hands-on centralized training on the SBIRT intervention and how to integrate it into their current work at sites. They will receive specialized training on the treatment component of SBIRT – varenicline use. They will be taught how to screen participants for their eligibility to receive varenicline, how to prescribe it and how to monitor participant adherence and side-effects. They will also receive training on the tools they need to complete -the adherence tool and adverse events tool.

In-service training will be conducted for all licensed clinicians eligible to prescribe varenicline - the nurse prescribers/dispensers, which will be scheduled and led by [name] but provided by Implementation leaders. The in-service will provide the background and orientation to treatment with varenicline. These in-service trainings will be repeated at each clinic (at different days and times) to accommodate diverse staff schedules.

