| 5. | 
Since your last study visit, have you ever quit for a period of at least 24 hours?
 
If No, skip to Q9.
                                                                                                                                                                                                                                                                                    |  Yes
 No                                                                                                                                                                                                                                                                                                   |
| 6. | 
Since your last study visit, how many times have you quit for at least 24 hours? (If more than 9 times, put 9)
                                                                                                                                                                                                                                                                                         | 
_____ times
                                                                                                                                                                                                                                                                                                                                            |
| 7. | 
After your most recent quit attempt, how long did you stay off cigarettes?
                                                                                                                                                                                                                                                                                                                             |  1-2 days
 A week
 2-4 weeks
 Over 4 weeks                                                                                                                                                                                                           |

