| 8. | 
While trying to quit, how serious have each of the following problems been for you?
 
(Use key below)
 
1 = Not at all
 
2 = A little
 
3 = Moderately
 
4 = Very
 
5 = Extremely
                                                                                                                                              |                                                                                                                                                                                                                                                                                                                                                               |
|    | 
 
▪ Weight gain
 
▪ Increased eating
 
▪ Digestive problems
 
▪ Nausea
 
▪ Headaches
 
▪ Drowsiness
 
▪ Depression or low mood
 
▪ Fatigue
 
▪ Insomnia
 
▪ Difficulty concentrating
 
▪ Heart pounding, or sweating
 
▪ Irritability
 
▪ Restlessness
 
▪ Anxiety
 
 | 
1   2   3   4   5
 |

|                                                                                  |                                                                                                                                                                                                                                                                                                                                                                                                                                                                                                                                                                                                                                                                    |             |

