## Appendix C5: BSMART Side-effects Checklist

### BSMART Side Effect Checklist

|                            |                        |
|----------------------------|------------------------|
| Researcher ID:      | Participant ID: |
| District:           | Facility:       |
| Date: (dd/mon/yyyy) |                        |

|                                        |                                        |                                        |                                        |                                        |                                         |
|----------------------------------------|----------------------------------------|----------------------------------------|----------------------------------------|----------------------------------------|-----------------------------------------|
| Week Number:                    |                                        |                                        |                                        |                                        |                                         |
|  Week 1 |  Week 2 |  Week 3 |  Week 4 |  Week 8 |  Week 12 |

Ask the participant if he/she experienced these side effects in the last week. If participant endorses a side effect, then ask if it was mild, moderate or severe. If participant endorses a side effect, also ask how often it happened and if they took any medications for it or called a doctor. Make any notes at the back of this form. Use the following format: "Did you experience nausea in the last week?" If yes, continue with: "Would you say the nausea was mild, moderate or severe? How often did you experience nausea in the last week? Did you take any medications or call a doctor for your nausea in the last week?"

| Side Effect                    | None
(0)              | Mild
(1)              | Moderate
(2)          | Severe
(3)            | Not
Rated
(4)      | Missing
(99)          | Related to Medication:
A = None; B = Remote;
C = Possible; D = Probable;
E = Missing                                          |

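### The varenicline side-effect checklist never asks about the mood and suicidality symptoms that trigger stopping, and two sections disagree on whether suicidal ideation ends trial participation

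*Protocol*

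**What the plan says.** Protocol section 3, Potential Risks to Subjects, lists the rarer varenicline effects: "Also in rare cases, changes in behavior, hostility, agitation, depressed mood, suicidal thoughts/actions, rash, and sensitivity reactions have occurred". It then commits the trial to watch for them: "We will closely monitor for depressive and other neuropsychiatric symptoms". The means is a form used at dispensing: "Each time a participant receives their medication, the prescribing clinicians will assess for adverse side effects using a standardized questionnaire". The action rule follows: "If a participant reports depressed mood or suicidal ideation, the participant will receive an immediate evaluation by a qualified clinician". Varenicline is then stopped, and whether the person stays in the study is settled between clinician, research team and participant.

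The nurse training section names the nurses' forms: "They will also receive training on the tools they need to complete -the adherence tool and adverse events tool". Appendix C5 is the only side-effect form shown. Its instruction is "Ask the participant if he/she experienced these side effects in the last week", and its boxes are for weeks 1, 2, 3, 4, 8 and 12.

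Appendix B4, given by research assistants at weeks 4, 12 and 24, includes "Depression or low mood" in question 8. Question 5, on whether the person has quit for 24 hours, carries the instruction "If No, skip to Q9".

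Criteria for Stopping says that observed suicidal ideation or intent activates the suicide prevention plan and that the participant is withdrawn.

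**The concern.** The action rule depends on finding the symptoms, and the form meant to find them does not ask about them. A nurse who completes C5 in full at every pick-up has asked about toothache, bruising and tinnitus, but not about low mood or suicidal thoughts. The Protocol rates the research as greater than minimal risk, and the varenicline exclusions in Appendix C3 contain no specific psychiatric criterion, only a general judgment of medical stability. Detection during treatment therefore carries more of the load. C5 also has no baseline box, so it offers no reference point for judging whether symptoms have worsened.

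The second problem is that two sites could treat the same event differently. One would take a participant with suicidal ideation out of the study. The other could keep that participant and obtain the week-24 smoking status and CO reading. The primary analysis is by intention to treat, so it needs that outcome.

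**Working it through.** The Protocol gives no figure to reproduce. The check is a comparison of lists and schedules.

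**Effects named against effects prompted.** Section 3, under varenicline, names 12 effects.

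| Effect | C5 item |
|---|---|
| Nausea | 1 |
| Vomiting | 2 |
| Constipation | 3 |
| Abnormal dreams | 13 |
| Rash | 36 |
| Sensitivity reactions | 37 (urticaria) |
| Flatulence | none |
| Behaviour change | none |
| Hostility | none |
| Agitation | none |
| Depressed mood | none |
| Suicidal thoughts or actions | none |

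C5 prompts for 6 of 12. Of the 6 missing, 5 are the mood, behaviour and suicidality effects (0 of 5 covered) and 1 is flatulence. Items 1 to 40 run without a gap, so no item was lost in reading the file. The nearest items are 5 (attention), 12 to 15 (sleep and dreams) and 23 (restlessness). Items 41 to 44 are blank lines and 45 is for comments.

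**When a printed form asks about low mood.**

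- Safety checks after baseline (item 8 of Estimating process and outcome measures): weeks {1, 2, 3, 4, 8, 12}, 6 in all.
- B4 visits: weeks {4, 12, 24}.
- Overlap: {4, 12}, so at most 2 of 6. For a participant with no 24-hour quit since the last visit, question 8 is skipped and the count is 0 of 6.
- Suicidal thoughts: no form shown asks, so 0 of 6.
- Medication pick-ups after baseline: weeks {1, 2, 3, 4, 8}, from the dispensing schedule and item 7, which puts the last supply at week 8. Overlap with B4 is {4}, 1 of 5.
- The quit day is day 8, and Appendix C7 starts the full dose in week 2. Week 4 is about day 28, and 28 − 8 = 20 days. The first low-mood prompt thus comes about three weeks into full-dose treatment.

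**Two rules for suicidal ideation.**

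| Section | Drug | Trial participation |
|---|---|---|
| Criteria for Stopping | not separated from participation | participant withdrawn |
| 3. Potential Risks to Subjects | stopped | decided jointly |

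Both rules apply to a participant who reports suicidal ideation, and they give different answers on participation.

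**Monitoring schedule (minor).** Item 8 has baseline and weeks 1, 2, 3, 4, 8 and 12 (7 points). C5 has 6 boxes, lacking baseline. The adverse-event row of Table 3 has weeks 1 to 8 (8 points). Table 3 and item 8 differ at baseline and weeks 5, 6, 7 and 12, which is 5 points.

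**The case against.** The strongest reply is that monitoring does not rest on one form. Appendix C1 reproduces label text that lists depression, hostility, agitation and suicidal ideation and tells prescribers to observe for them, and varenicline is to be prescribed according to its labelling. Nurses are trained on the effects of quitting, which include depression and anxiety. Participants are told about side effects. The data and safety monitoring plan requires adverse events to be collected at every follow-up visit. All of this stands, and it means the stopping rule works once a symptom is volunteered or seen. None of it puts a question to the participant.

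It can also be said that no text expressly identifies C5 as the standardized questionnaire, that the toxicity criteria in Appendix C2 and the full suicide prevention plan are not reproduced, and that the printed B4 lacks the varenicline questions the Protocol attributes to it. That is fair: the counts above describe printed prompts on the forms shown, not everything a participant may be asked. Item 8 uses the toxicity criteria to classify and grade events, which is not a prompt.

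Restlessness is close to agitation, and the intake questionnaire asks about coping over the past 30 days. Neither is one of the two triggers.

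On withdrawal, the stricter rule errs on the side of protection, and Criteria for Stopping does not say that outcome collection ends. Loss of the week-24 outcome is therefore an inference from the plain sense of the word. The conflict over continued participation remains.

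**Conclusion.** Both parts hold, and the point should be fixed. C5 prompts for neither of the two symptoms on which section 3 acts, and for none of the five mood, behaviour and suicidality effects that it names. The Protocol also gives two answers on whether suicidal ideation ends participation.

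This rests on C5 being the questionnaire used at dispensing, which is inferred because no other side-effect form is shown, and on reading withdrawal of the participant as withdrawal from the study. The effects are described as rare, so no material bias in the primary abstinence result is claimed. What is weakened is the detection of symptoms and the consistency of handling between sites. The Table 3 mismatch is a minor correction.

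**What to change.** 1. Add depressed mood, suicidal thoughts, hostility, agitation and behaviour change to C5 as prompted items, with wording set by the clinical team. Add a baseline box, since item 8 already requires a baseline check.
2. Give Criteria for Stopping and section 3 the same rule: suicidal ideation stops varenicline and activates the suicide prevention plan, while leaving the trial is a separate decision. Keep the week-24 smoking and CO visit for those who still consent.
3. Match the adverse-event row of Table 3 to item 8 and C5: baseline and weeks 1 to 4, 8 and 12. No pick-up falls in weeks 5 to 7. If contact is wanted then, item 8 and C5 should say so.
4. Optionally, show adverse-event collection in Table 2 at weeks 4, 12 and 24.

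The cost is about five lines and a box on one form, one table row, one aligned rule, a short addition to the existing three-day nurse training, and approval by the two ethics committees. Every check falls on a contact already scheduled, so no visit is added.
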